### Primary and secondary outcomes

#### Primary outcome

Abnormal myocardial perfusion reserve (global MPR <2.0).

#### Secondary outcomes

A summary of the secondary outcomes is shown in Box 1.

Box 2.CorCMR substudy secondary outcomes and analysesLV volumes, function and massLV EFLVEDVLV EDV indexLV ESVLV ESV indexLV massLV mass indexLV COLV CO indexAtrial areaLeft atrial area (cm^2^)Left atria dilated (Y/N)Right atrial area (cm^2^)Right atria dilated (Y/N)Qualitative perfusion analysisAbnormal perfusion (Y/N)Number of abnormal segments (n)Transmurality of perfusion defects (%)Pattern (epicardial, microvascular, mixed and equivocal)Quantitative perfusion analysisGlobal MPR <2.0 (Y/N)Segmental/AHA MPRGlobal stress and rest MBFSegmental/AHA territory stress and rest MBFGlobal stress endocardial:epicardial MPR ratioSegmental/AHA territory endocardial:epicardial MPR ratioPerfusion dyssynchrony analysisMyocardial perfusion dyssynchrony index (variance and coefficient of variation of the time to maximum signal intensity upslope and time to peak myocardial signal intensity enhancement)Adenosine vasodilator stress responseSplenic switch-off (Y/N)HR and BPchangeRate-pressure product at rest and stressLate gadolinium enhancement imagingAbnormal LGE (Y/N).Number of affected AHA segments (n)Pattern of abnormal LGE (ischaemic and non-ischaemic)Myocardial infarct scar burden (transmurality, infarct mass, infarct mass as percentage LV mass)Native T1 and ECV mappingNative T1 (global and midseptal values)ECV (global and midseptal values)Myocardial strainFeature-tracking and DENSE (two methods)Longitudinal strain (global and by AHA segment)Circumferential strain (global and by AHA segment)Radial strain (global and by AHA segment)Incidental findingsPresent (Y/N)Clinically significant (Y/N)Associations of abnormal perfusion with baseline characteristicsSex, age and traditional CAD risk factorsCAD risk scores (JBS3 and ASSIGN)Gensini score of epicardial plaque burdenAssociations of abnormal perfusion with invasive coronary artery function testing dataAssociation of myocardial perfusion with IMR, CFR, RRR and endothelial function testing (continuous and binary)Subset of patients with multivessel invasive coronary artery function measurementsAssociation with clinical diagnosis (ANOCA disease endotype)Associations of abnormal perfusion with baseline CMR dataLV volumes and massMyocardial strainNative T1 relaxation time and ECVPresence of LGEDiagnostic accuracyDiagnostic accuracy of quantitative perfusion CMR to detect abnormal IMR, CFR, RRR and endothelial dysfunctionAHA, American Heart Association; ANOCA, angina with no obstructive coronary artery disease; BP, blood pressure; CFR, coronary flow reserve; CAD, coronary artery disease; CO, cardiac output; CorCMR, Coronary Microvascular Angina Cardiac MRI; EF, ejection fraction; EDV, end-diastolic volume; ESV, end-systolic volume; ECV, extracellular volume; HR, heart rate; IMR, index of microcirculatory resistance; LV, left ventricular; LGE, late gadolinium enhancement; MBF, myocardial blood flow; MPR, myocardial perfusion reserve; RRR, relative resistance ratio,

### Statistical analyses

The CorMicA trial has a comprehensive statistical analysis plan that governs all statistical aspects of the study authored by the trial statistician. The statistical analysis plan includes the prespecified CorCMR substudy that is designed to assess for associations between CMR measures and invasive measures and endotypes (reference dataset). Continuous outcomes will be analysed using linear regression with adjustment for baseline levels where available. Where continuous data are clearly not normally distributed, standard transformations will be applied to achieve approximate normality prior to analysis. Appropriate alternative regression methods will be applied to other types of data (eg, logistic regression for binary outcomes).

#### Sample size calculation

The primary outcome is the proportion of patients with an MPR<2.0. The proportion of patients with microvascular angina defined by invasive endotyping will be assessed. We will further assess the MPR ratio with the highest AUC for microvascular angina classified invasively.

Considering the correlation between CFR measured invasively and MPR measured non-invasively within the common territory of a major epicardial coronary artery, then a sample size of 110 subjects would enable a minimum clinically significant correlation of 0.3 to be detected with 90% power at a 5% significance level. If only 60 subjects have available data, then 80% power would be available to detect a correlation of 0.37 at the 5% level.

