### Literature review

Patients with confirmed microvascular or vasospastic angina have a precise diagnosis of the underlying disease endotype, and pharmacotherapy may be commenced as appropriate. Conversely, patients with normal invasive coronary artery function tests may have antianginal therapy appropriately discontinued, and alternative causes of chest pain investigated. In comparison with invasive tests of coronary artery function, non-invasive CMR imaging may be more attractive to patients, but at present, the role of CMR in the diagnostic work-up of patients is uncertain. CorCMR will provide data on the role of CMR in the diagnosis of patients with ANOCA. Traditional non-invasive ischaemia testing in patients with ANOCA has provided mixed results. Panza *et al*^23^ investigated the yield of non-invasive ischaemia testing in 70 patients with ANOCA. Patients underwent exercise ECG testing, radionuclide angiography, myocardial perfusion scintigraphy and dobutamine stress echocardiography. Abnormal test results were detected in 31%, 16%, 18% and 0% respectively, with no concordance between the test results. This led to the conclusion that patients with ANOCA did not have inducible myocardial ischaemia as a cause for their symptoms. However, there is evidence that perfusion CMR may detect abnormalities of MBF in patients with ANOCA. Panting *et al*^26^ first described the use of adenosine stress perfusion CMR in patients with ANOCA. Twenty patients with syndrome X and 10 control subjects were included, and subendocardial hypoperfusion was demonstrated in patients with syndrome X using a semiquantitative perfusion metric. A subset of 118 women with ANOCA enrolled in the National Heart, Lung and Blood Institute-sponsored multicentre Women’s Ischemic Syndrome Evaluation (WISE) study underwent stress perfusion CMR and invasive microvascular function testing with Doppler wire-derived CFR and endothelial function testing with intracoronary acetylcholine.^29^ Stress perfusion CMR was also performed in 21 asymptomatic control subjects. Reduced global MPRi was found in patients with ANOCA compared with controls (1.79 vs 2.23, p<0.0001), and a lower MPRi was predictive of ≥1 abnormal invasive coronary vascular function metric (OR=0.78, p<0.0001). An MPRi threshold of 1.84 predicted an abnormal invasive coronary function metric with sensitivity of 73% and specificity of 74%. Qualitative analysis of the perfusion studies found no significant differences between the study and control groups (summed segments with abnormal perfusion 6.66 vs. 4.45, p=0.09), suggesting that quantitative perfusion analyses may have greater sensitivity for abnormal perfusion in patients with ANOCA.

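### The fallback power figure is slightly wrong: 60 patients give about 84% power at r = 0.37, and 80% power corresponds to r of about 0.355

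*Protocol article*

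**What the plan says.** The Sample size calculation section of the protocol article opens by identifying the primary outcome: "The primary outcome is the proportion of patients with an MPR<2.0". The Primary outcome section defines it at whole-heart level: "Abnormal myocardial perfusion reserve (global MPR <2.0".

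The power statements that follow concern a different quantity: "Considering the correlation between CFR measured invasively and MPR measured non-invasively within the common territory of a major epicardial coronary artery". For this correlation, "a sample size of 110 subjects would enable a minimum clinically significant correlation of 0.3 to be detected", with 90% power at the 5% level. The fallback reads: "If only 60 subjects have available data, then 80% power would be available to detect a correlation of 0.37 at the 5% level".

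The section does not state the type of coefficient, the sidedness of the test or the method. It gives no expected value or precision for the primary proportion.

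**The concern.** The two power statements stand side by side, concern the same correlation and use the same significance level, so one method should give both. The method that gives the first does not give the second. Anyone who judges whether 60 scans would be enough is working from a detectable correlation that does not match its stated power.

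A lesser matter sits in the same section. It names a proportion as primary, yet the only quantity sized is a territory-level correlation, which belongs among the secondary analyses (association of perfusion with CFR). A reader therefore cannot see how precisely the primary outcome will be estimated, or what falling from 110 to 60 patients does to that precision.

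**Working it through.** **Inputs.** From the Sample size calculation section: n = 110, r = 0.30, power 90%; n = 60, r = 0.37, power 80%; significance level 5%. Assumed because not stated: a two-sided test of r = 0 on a Pearson-type coefficient. This fits the Statistical analyses section, which plans linear regression with transformation towards normality.

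**Formula.** Power = Φ(atanh(r)·√(n − 3) − 1.96).

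**Step 1: the main figure.** atanh(0.30) = 0.3095 and √107 = 10.344. Their product is 3.202; less 1.96 this is 1.242, and Φ(1.242) = 89.3%. A simulation of 200,000 bivariate normal samples gives 89.6%. The n for exactly 90% is ((1.96 + 1.2816)/0.3095)² + 3 = 112.7, so 113. The stated 90% at n = 110 is right to rounding.

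**Step 2: the fallback by the same method.** atanh(0.37) = 0.3884 and √57 = 7.550. Their product is 2.932; less 1.96 this is 0.972, and Φ(0.972) = 83.5%. With a bias correction or a t-based critical value it is 84.0%; by simulation, 84.1%. The stated figure is 80%.

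**Step 3: what 80% power corresponds to.**
- Detectable correlation at n = 60: tanh((1.96 + 0.8416)/√57) = tanh(0.371) = 0.355.
- Sample size for r = 0.37: (2.8016/0.3884)² + 3 = 55.02, so 56 patients.

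**Step 4: likely source.** The value 0.371 in step 3, before the back-transformation, rounds to the printed 0.37. For n = 110 the z-scale value is (1.96 + 1.2816)/√107 = 0.313, which back-transforms to about 0.30, the value printed. The fallback appears to be on the z scale and the main figure on the correlation scale.

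**Step 5: does another method give both figures?**

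| Method | n = 60, r = 0.37 (stated 80%) | n = 110, r = 0.30 (stated 90%) |
|---|---|---|
| Fisher z, two-sided | 83.5% | 89.3% |
| Fisher z, one-sided | 90.1% | 94.0% |
| Noncentral t (regression) | 85.8% | 90.5% |
| Spearman variance (two forms) | 81.0–81.3% | 87.5–87.9% |
| r not transformed, √(n − 3) | 79.8% | 87.4% |

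None of these gives both. The last two come close to 80% for the fallback but miss 90% for the main figure by 2 to 3 points.

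**Step 6: precision of the primary proportion.** Half-width of the 95% interval = 1.96·√(p(1 − p)/n). The article gives no expected p, so a range of 20% to 50% is assumed.

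| n | p = 20% | p = 50% |
|---|---|---|
| 110 | 7.5 points | 9.3 points |
| 60 | 10.1 points | 12.7 points |

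At any p, going from 110 to 60 patients widens the interval by √(110/60) = 1.35, about a third.

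**The case against.** The strongest defence is that the slip does no harm. It understates power, so 60 patients do give at least 80% power at r = 0.37, and no enrolment target or analysis depends on the figure. The method is not stated either, and an untransformed or rank-based calculation comes close to 80%. The first part stands and limits the weight of the point. The second does not rescue the figure, because those methods then fail on the 110-patient statement in the same paragraph.

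On the primary outcome, the defence is that a descriptive proportion has no hypothesis to power, that recruitment is bounded by the 150 patients randomised in the parent trial, and that the Statistical analyses section says the substudy is designed to assess associations. The expected precision may also be in the full analysis plan, which is not at hand. All of this is fair, and it makes this part secondary.

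A reader might go further and infer that a target of 0.3 is too weak for the aim of diagnostic validity, or that a significant correlation would be taken as validation. The article does not support this. A smaller target correlation needs more patients, not fewer, and nowhere is rejecting r = 0 made the test of validity. The Aims section plans concordance with the invasive endotypes, AUC and diagnostic accuracy; the secondary outcomes list diagnostic accuracy separately; and the article commits to STARD reporting.

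**Conclusion.** The fallback statement is wrong as printed. By the method that reproduces the main figure, power at n = 60 and r = 0.37 is about 84% rather than 80%, and the correlation detectable with 80% power is about 0.355 rather than 0.37. This assumes a two-sided test and a Pearson-type coefficient. The missing back-transformation is an inference from the match at 0.371; the article does not show its working.

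The error is about 4 points of power, in the safe direction. It would be wrong to infer that the substudy is underpowered, or that the 110-patient statement is also in error: 89.3% to 89.6% against 90% is rounding.

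That the section sizes a secondary correlation and not the primary proportion is true, but it is an incompleteness of presentation. The half-widths in step 6 do not show the sample to be inadequate, and they rest on an assumed proportion of 20% to 50%.

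**What to change.** In the Sample size calculation section, either replace 0.37 with 0.355 or keep 0.37 and state about 84% power. Leave the 110-patient statement as it is. State that the test is two-sided and name the coefficient, so that both figures can be checked.

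Add a sentence saying that the calculation concerns the secondary CFR–MPR correlation, and give the expected 95% interval half-width for the primary proportion: about 7.5 to 9.3 points with 110 patients and 10.1 to 12.7 with 60, for a proportion between 20% and 50%.

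The cost is rewording one section. Enrolment, data collection and the planned analyses do not change.

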## Discussion

The British Heart Foundation CorMicA trial will assess a routine stratified medicine strategy in a large cohort of prospectively enrolled patients with ANOCA. The prespecified CorCMR substudy will involve comprehensive invasive tests of coronary artery function paired with multiparametric perfusion CMR studies. The analysis will provide information on the diagnostic value of quantitative pixel-wise mapping of myocardial perfusion in this population.

Contemporary guidelines recommend functional testing, including with CMR, to assess for myocardial ischaemia in patients in whom multidetector CT coronary angiography has shown CAD of uncertain functional significance or is non-diagnostic.^49^ Increasingly, patients are referred to the catheter laboratory based on the results of anatomical imaging using CT coronary angiography or with no prior tests based on symptoms and a high likelihood of CAD.^49 50^ The CorCMR substudy in CorMicA aims to inform this gap.

The CorCMR substudy will be performed on a 1.5 Tesla MRI scanner. In comparison, 3.0 Tesla imaging permits improved signal-to-noise ratio and provides higher in-plane spatial resolution perfusion imaging.^51 52^ However, CMR imaging in the NHS is most widely performed at 1.5 Tesla, hence the results from CorCMR are clinically relevant and transferable.

### Literature review

Patients with confirmed microvascular or vasospastic angina have a precise diagnosis of the underlying disease endotype, and pharmacotherapy may be commenced as appropriate. Conversely, patients with normal invasive coronary artery function tests may have antianginal therapy appropriately discontinued, and alternative causes of chest pain investigated. In comparison with invasive tests of coronary artery function, non-invasive CMR imaging may be more attractive to patients, but at present, the role of CMR in the diagnostic work-up of patients is uncertain. CorCMR will provide data on the role of CMR in the diagnosis of patients with ANOCA. Traditional non-invasive ischaemia testing in patients with ANOCA has provided mixed results. Panza *et al*^23^ investigated the yield of non-invasive ischaemia testing in 70 patients with ANOCA. Patients underwent exercise ECG testing, radionuclide angiography, myocardial perfusion scintigraphy and dobutamine stress echocardiography. Abnormal test results were detected in 31%, 16%, 18% and 0% respectively, with no concordance between the test results. This led to the conclusion that patients with ANOCA did not have inducible myocardial ischaemia as a cause for their symptoms. However, there is evidence that perfusion CMR may detect abnormalities of MBF in patients with ANOCA. Panting *et al*^26^ first described the use of adenosine stress perfusion CMR in patients with ANOCA. Twenty patients with syndrome X and 10 control subjects were included, and subendocardial hypoperfusion was demonstrated in patients with syndrome X using a semiquantitative perfusion metric. A subset of 118 women with ANOCA enrolled in the National Heart, Lung and Blood Institute-sponsored multicentre Women’s Ischemic Syndrome Evaluation (WISE) study underwent stress perfusion CMR and invasive microvascular function testing with Doppler wire-derived CFR and endothelial function testing with intracoronary acetylcholine.^29^ Stress perfusion CMR was also performed in 21 asymptomatic control subjects. Reduced global MPRi was found in patients with ANOCA compared with controls (1.79 vs 2.23, p<0.0001), and a lower MPRi was predictive of ≥1 abnormal invasive coronary vascular function metric (OR=0.78, p<0.0001). An MPRi threshold of 1.84 predicted an abnormal invasive coronary function metric with sensitivity of 73% and specificity of 74%. Qualitative analysis of the perfusion studies found no significant differences between the study and control groups (summed segments with abnormal perfusion 6.66 vs. 4.45, p=0.09), suggesting that quantitative perfusion analyses may have greater sensitivity for abnormal perfusion in patients with ANOCA.

CorCMR will inform the nascent evidence on the presence and magnitude of associations between invasive and non-invasive assessments of coronary vascular function. Liu *et al* compared semiquantitative perfusion CMR against IMR measurement in 50 patients with ANOCA and 20 age-matched healthy control subjects.^30^ In a ROC analysis, an MPRi threshold of 1.4 was optimal for the detection of myocardium with inducible ischaemia in patients with obstructive epicardial CAD (FFR ≤0.8) and in patients with ANOCA. Similarly, Williams *et al*^31^ performed semiquantitative perfusion CMR and measured thermodilution and Doppler flow wire-derived metrics of microvascular resistance (IMR and hyperaemic microvascular resistance (hMR), respectively) in a heterogeneous cohort of 54 patients (44 with acute myocardial infarction and 10 with stable angina). Microvascular function testing was performed in unobstructed epicardial coronary arteries (FFR >0.8). MPRi correlated with hMR (r=0.58, p<0.001) but not IMR (r=−0.27, p=0.15). These comparisons are between a non-invasive metric of vasodilatory capacity (MPRi) and an invasive metric of microvascular resistance (IMR and hMR), which may more specifically reflect fixed structural changes in the microcirculation (rather than vasodilator capacity).

CMR permits the reference-standard non-invasive assessment of myocardial tissue characterisation. CorCMR will provide data on diffuse interstitial fibrosis, ECV and myocardial scar. The role of T1 mapping and ECV analysis in patients with ANOCA is uncertain. In a substudy of the iPOWER natural history study, 54 women with ANOCA underwent native T1 mapping and ECV analysis, PET-derived MBF measurement, and transthoracic Doppler echocardiography CFR assessment.^53^ There was no correlation found between abnormal coronary vascular function as revealed by PET or echocardiography-derived CFR, and myocardial native T1 or ECV. Occult myocardial infarction in patients with ANOCA may be clinically relevant. In a substudy of the WISE cohort, Wei *et al*^54^ performed CMR imaging in 340 female patients with ANOCA. A total of 26 patients (8%) had hyperenhancement on LGE imaging, with 18 patients having evidence of occult myocardial infarction (mean scar size 5.1 g), and 8 patients had a non-ischaemic pattern (mean scar size 8.9 g).

